### Variables of the study

#### Infant neurodevelopment (outcome 1)

Neurodevelopment is assessed using the Bayley Scales of Infant Development (BSID-III) at the 6th and 12th month after childbirth (with a margin of 15 days either way from the exact date). The scale is administered by a trained professional (psychologist) from Pearson. This instrument is designed for assessing children aged 1–42 months and comprises the following scales: (i) Cognitive Scale, evaluating sensory-motor development, exploration and manipulation, concept formation, and memory; (ii) Language Scale, consisting of items for receptive and expressive communication, forming two distinct sub-tests; (iii) Motor Scale, assessing overall motor skills and fine motor abilities; (iv) Socio-Emotional Scale, identifying key milestones in social and emotional development at specific ages; (v) Adaptive Behavior Scale, accessing the child’s functional daily life skills, considering communication, home life, health, safety, and leisure.

Additionally, members of the project team assess the developmental milestones recorded in the Child’s Health Record. This assessment is routinely conducted in the pediatric clinic, and its validity, as compared to the results of the BSID-III (gold standard), will provide another valuable piece of data generated by the current study.

#### Maternal mental health (outcome 2)

Maternal mental health is monitored in all waves of follow-up: up to 15 days, 2, 6, and 12 months postpartum. During the first appointment, data are collected regarding the postpartum mother’s history of depression, as well as her family history of depression. A validated version of the Edinburgh Postnatal Depression Scale (EPDS) is employed. The EPDS was developed by Cox et al. [35] and translated and validated into Portuguese by Santos et al. [36] and consists of a self-report instrument composed of 10 statements, with scored options from 0 to 3 based on the presence and intensity of depressive symptoms.

Many studies cite and use the EPDS because it is a questionnaire that is easy to administer and understand for women, and it has proven to be highly effective in identifying postpartum depression [37–40]. At baseline, the EPDS will be administered by trained interviewers (health professionals or undergraduate students in the healthcare field). In the subsequent follow-ups, participants will receive the EPDS online, via email and/or messaging app, seven days before the in-person meeting, allowing them to self-complete the questionnaire. If a participant does not respond to the online questionnaire, the scale will be administered by trained interviewers on the day of the in-person meeting.

Additionally, depression is assessed using the Beck Depression Inventory-II (BDI-II) at 6 and 12 months postpartum. This is because the validation of the Brazilian version of the EPDS was only conducted with women up to 3 months postpartum. The BDI-II is a widely used instrument worldwide and has been validated for the Brazilian population [41]. The application will be conducted by a trained psychologist.

#### Maternal blood and breast milk samples (main exposure)

Human milk (a minimum of 10 ml and a maximum of 20 ml) is obtained using an electric breast pump. These samples are stored and transported under refrigeration within a maximum of 2 hours to the location for analysis. The samples are homogenized using a vortex (1 minute), divided into aliquots, and stored at -30°C for a maximum of 24 hours, after which they are moved to final storage at -80°C, where they remain until processing and analysis. Samples are collected at every follow-up visit or until the breastfeeding mother no longer has milk.

Blood samples are collected at visits T0, T2, and T3 in collection tubes containing EDTA. The samples are centrifuged (3500 rpm/15 minutes), and the plasma is separated into aliquots and stored in a freezer at -30°C for a maximum of 24 hours, after which they are transferred to final storage at -80°C, where they remain until processing and analysis. Commercial ELISA kits are used to determine the concentration of adiponectin and leptin in both breast milk and plasma.

In addition to adipocytokines, inflammatory biomarkers, including non-enzymatic oxidized metabolites of polyunsaturated fatty acids and species of phospholipids and triacylglycerols, as well as vitamin D metabolites, will be investigated. The oxidized metabolites and vitamin D metabolites will be analyzed through targeted lipidomics using a QTrap mass spectrometry platform (AB Sciex QTRAP 5500) [42], and lipid species through high-resolution semi-targeted lipidomics on an Orbitrap platform (Q-Exactive, Thermo-Finnigan) [43].

#### Socioeconomic, demographic, lifestyle, and reproductive history variables

A structured questionnaire will be applied to determine maternal socioeconomic and demographic characteristics, as well as lifestyle and reproductive data that are part of the mother’s history: age, marital status, number of children, occupation, level of education, place of residence, type of housing, smoking, alcohol consumption, social support, newborn’s sex, number of births, date of the last birth, type of delivery (specifying the reason for the surgical delivery, when applicable), and duration of pregnancy.

Social support is estimated through two simple questions at T1 and T2: "Do you share baby care with someone?" (response options: yes, no) and "How often do you have someone to help you if you are very tired or sick?" (response options: never, rarely, sometimes, almost always, always). At T3, social support is measured using the Portuguese version of the social support questionnaire from the Medical Outcomes Study [44]. This instrument assesses the perceived availability of support when needed and consists of four dimensions: material, affective, positive social interaction, and emotional/informational. The instrument comprises 19 questions with responses ranging from 1 (never) to 5 (always) points. Therefore, social support is measured by summing the responses, and the higher the score, the greater the estimated social support.

#### Maternal and infant anthropometry

At the first appointment, data on the woman’s pre-pregnancy weight will be collected. Preference will be given to the weight measured up to the 13th week of pregnancy recorded in the pregnant woman’s follow-up booklet. If this record is nonexistent, the reported weight will be recorded. For the newborn, the following data contained in the Child Health Handbook will be collected: birth weight, length at birth, head circumference at birth, and Apgar scores at 1 and 5 minutes.

For the assessment of the body composition of postpartum women (in all follow-ups) and infants (T0 and T1), the air displacement plethysmography method will be used. This method evaluates body volume and density by measuring the volume of air displaced by the body inside a closed chamber. It is a relatively recent, fast, safe, and comfortable method [45]. This technique is based on Boyle’s law, which relies on the inverse relationship between pressure and volume to determine body composition. Once this volume is defined, it is possible to apply the principles of densitometry to determine body composition by calculating body density [46]. The plethysmograph, also known as the BOD POD for adults or PEA POD for infants, is connected to a computer that calculates variations in air volume and pressure inside the empty and occupied chamber. This equipment makes adjustments for lung variables required in estimating body volume. The equipment also provides the weight of the woman and the child during each assessment. Women undergo the assessment wearing tight-fitting clothing, such as a top and shorts or a swimsuit, and they use a swim cap to secure their hair. Infants are assessed without clothing and wear a stocking cap on their heads, regardless of whether they have hair or not.

Maternal height will be directly assessed using a wall-mounted compact stadiometer (WISO®) with a precision of one millimeter during the first follow-up wave.

Starting from T2, the child’s weight will be measured using a digital pediatric scale with a maximum capacity of 20kg or on the scale integrated with the PEA POD. The child’s length will be measured using an infantometer, with the child lying down and their head supported on the fixed part of the instrument. The movable part will be appropriately positioned under the child’s feet. Measurements will be taken in duplicate, and the average of the measurements will be used. Additionally, the child’s fronto-occipital head circumference will be measured using a non-stretchable measuring tape, corresponding to the maximum head circumference.

#### Breastfeeding and infant dietary intake

The frequency of breastfeeding will be estimated in all follow-ups using a structured questionnaire adapted from the II Breastfeeding Prevalence Survey in Brazilian Capitals and the Federal District, conducted by the Ministry of Health [47]. The questionnaire also assesses the introduction of solid foods by inquiring about the consumption of porridge, fruits, savory foods, beans, meats, vegetables, greens, and ultra-processed foods.

#### Maternal dietary intake

The dietary intake of ultra-processed foods will be assessed in all follow-up waves using the NOVA score [48]. This is a self-administered questionnaire that takes around three minutes to complete and has shown good performance in estimating the consumption of ultra-processed foods in the Brazilian diet. The questionnaire will be sent electronically (via email or WhatsApp) one week before the in-person consultations (except for the first consultation). For women who do not respond to the electronic questionnaire, it will be administered during the in-person consultation.

The overall dietary intake of postpartum women is assessed in the third follow-up (T3) using a 24-hour dietary recall proposed by Neri et al. (2023) (Nova24h, Portuguese version) [49]. It’s a self-administered web-based instrument designed to categorize food intake according to the Nova groups. The Nova24h will be applied on two non-consecutive days to estimate habitual consumption. The first dietary recall will be sent via email prior to the T3 consultation. The second will be completed on the day of the T3 consultation. Dietary data will be entered into the Nutrabem Pro®14 software to obtain energy, macro, and micronutrient values.

#### Sleep quality

The quality of sleep will be assessed using the Pittsburgh Sleep Quality Index, translated and validated for the Brazilian population (PSQI-BR) [50]. In the first wave of follow-up (up to 15 days postpartum), the questions will relate to the gestational period. In the subsequent waves, women will be asked to respond based on the current period. The questionnaire will be sent electronically (via email or WhatsApp) one week before the in-person appointments (except for the first appointment). For women who do not respond to the electronic questionnaire, it will be administered during the in-person appointment.

#### Mother-infant emotional bond

The mother-infant emotional bond will be assessed in the second and third follow-up waves (T1 and T2) through the translated version of the Postpartum Bonding Questionnaire (PBQ) [51]. The PBQ was originally developed by Brockington & Wilson and consists of 25 items divided into four factors: overall emotional bonding, rejection and anger towards the baby, anxiety directed towards the baby, and the risk of abuse [52]. Participants rate their level of agreement with the statements on Likert scales ranging from 0 (always) to 5 (never). The questionnaire will be sent electronically (via email or WhatsApp) one week before the in-person consultations. For women who do not respond to the electronic questionnaire, it will be administered during the face-to-face consultation.

#### Participant support

The occurrence of depressive symptoms in women is the critical outcome that is expected to be more recurrent during the project’s follow-up. Women classified with depressive symptoms by the EPDS scale (≥ 13 points) or diagnosed with depression by the BDI-II are referred for care at the Mental Health Coordination of IFF (COJ) if they are enrolled at IFF. Participants who are not enrolled at IFF are referred for care at the outpatient clinic of the Institute of Psychiatry of the Federal University of Rio de Janeiro (IPUB). Naturalistic medical and psychological treatment will be provided according to the postpartum period and the patient’s symptoms.

In the case of other critical outcomes, the project team is responsible for ensuring that participants receive appropriate care. It is worth noting that the team is multidisciplinary, consisting of professionals from the fields of pediatrics, psychiatry, neonatology, psychology, nutrition, and nursing.

The total amount spent on transportation and meals related to participation in the project is reimbursed to the participants.

### Sample size

To assess differences in adipocytokines in human milk according to infant development, the reference was the global score of cognitive development in the communication domain. A previous study assumed that the standard deviation of the score is 13.6 for children of 6 months [53]. We will consider a difference of 3 points significant, and we aim for a significance level of 5% to detect differences if they exist.

Applying the formula for determining the sample size based on an estimate of the population mean, n=[(Zα/2.σ)/e]^2, where Z_α/2_ = 1.96, e = 3 and σ = 13.6 (standard deviation), we obtain N = 79 [54]. If we estimate a follow-up loss of approximately 35%, the sample size (N) should be 117 mother-child pairs.

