Additionally, considering the need for more evidence on the association between adipokines and depression, the lack of studies on this topic in postpartum women, and the impact of depression on maternal and child health, assessing the association between adipokines and maternal mental health is a pathway to explore new strategies for preventing and treating postpartum depression. If the hypothesis is confirmed, clinicians could consider monitoring adiponectin and leptin levels in maternal plasma as potential biomarkers for maternal mental health and infant neurodevelopmental outcomes. Furthermore, this research could inform guidelines for supporting breastfeeding mothers, emphasizing the importance of maternal nutrition and mental well-being for optimizing the neurodevelopment of the infant. Ultimately, this could lead to more personalized approaches in maternal and infant healthcare, where interventions are tailored based on the specific needs of both the mother and child.

The main limitations of this study are considered to be the potential losses of follow-up, which are inherent to longitudinal studies, and the relatively small sample size. While the sample size is sufficient for the primary objectives of the project (as indicated by the sample size calculation), some specific objectives may not be fully addressed, thereby increasing the risk of type II errors.

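### The sample size rests on a score that matches none of the Bayley-III scores the protocol describes, and the Discussion claims more from the calculation than it can support

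*Protocol article*

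**What the plan says.** The Sample size section gives its purpose as follows: "To assess differences in adipocytokines in human milk according to infant development". It then names the sizing variable: "the reference was the global score of cognitive development in the communication domain". The inputs are an SD ("A previous study assumed that the standard deviation of the score is 13.6 for children of 6 months"), a difference ("We will consider a difference of 3 points significant") and a 5% level. The method is described thus: "Applying the formula for determining the sample size based on an estimate of the population mean". The result is 79 pairs, raised to 117 for follow-up loss.

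The section on infant neurodevelopment (outcome 1) names the Bayley-III, given at 6 and 12 months, and lists five scales: Cognitive, Language, Motor, Socio-Emotional and Adaptive Behavior. Communication is placed in the second: "Language Scale, consisting of items for receptive and expressive communication, forming two distinct sub-tests". It appears again as one area of the Adaptive Behavior Scale. The description of the Cognitive Scale does not mention it.

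The Discussion concludes: "While the sample size is sufficient for the primary objectives of the project (as indicated by the sample size calculation".

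**The concern.** The SD and the 3-point difference are the only study-specific inputs to the 79. Both are in score units, so neither can be judged until the score is known. The label joins a cognitive score to a communication domain, and the protocol's own description keeps these on separate scales. A reader cannot tell whether 3 points refers to the Cognitive score, the Language score or a communication sub-test, nor whether 13.6 is the SD of that score.

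The direction is also unclear. The stated aim is a difference in adipokines between levels of development, yet the SD and the difference are those of a development score.

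What is at stake is the claim of sufficiency in the Discussion. It leans on this calculation for all primary objectives, but the calculation concerns one infant score that cannot be identified.

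**Working it through.** **1. The label against the instrument.**

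| Bayley-III scale as described under outcome 1 | Communication included? | A global cognitive score? |
|---|---|---|
| Cognitive | no | cognitive, but without a communication domain |
| Language | yes, two sub-tests | no |
| Motor | no | no |
| Socio-Emotional | no | no |
| Adaptive Behavior | yes, one area among several | no |

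No row meets both parts of the label. The Sample size section does not name the instrument, and the statistical analysis section speaks only of development scores in the plural, so neither settles which row is meant.

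**2. The plan's own figure.** Inputs from the Sample size section: Z = 1.96, σ = 13.6, e = 3.

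n = (Z·σ/e)² = (1.96 × 13.6 / 3)² = 78.95, rounded up to 79. The figure is reproduced.

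**3. What the formula delivers.** Solved for e, it is the half-width of a 95% interval for one mean:

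e = 1.96 × 13.6 / √79 = 3.00 points.

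It has no power term, no second group and no adipokine variable. Three points is 3/13.6 = 0.22 SD if 13.6 is the right SD.

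**4. How much depends on the SD.** The documents give no SD for any named Bayley-III score. The values below other than 13.6 are assumptions for illustration and are not attributed to particular scales. The margin e = 3 is kept, and n is rounded up.

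| SD | (1.96·SD/3)² | n | Half-width with 79 completers |
|---|---|---|---|
| 10 | 42.7 | 43 | 2.2 |
| 12 | 61.5 | 62 | 2.6 |
| 13.6 | 78.95 | 79 | 3.0 |
| 15 | 96.04 | 97 | 3.3 |
| 16 | 109.3 | 110 | 3.5 |

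Because n grows with the square of the SD, which score the SD describes is a material question.

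**5. Direction.** The section headings label infant neurodevelopment as outcome 1 and the blood and milk samples as the main exposure. The paragraph on the directed acyclic graph seeks the effect of plasma adiponectin on infant neurodevelopment, and the Introduction hypothesises that milk composition influences development. The Sample size section alone states the comparison the other way round. The mixed-model paragraph assigns no direction and supports neither side.

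**6. Scope of the sufficiency claim.** The objectives in the abstract cover the correlation of adipokines between plasma and milk, infant neurodevelopment at 6 and 12 months, and maternal mental health over the first year. The calculation uses one infant score at 6 months. It contains no input for the depression scales or for the correlation.

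**The case against.** The strongest reply is that this is loose, translated wording for the Language Scale. The SD is given for infants of 6 months, which is a Bayley-III visit, and the Language Scale is administered at that visit. The cited source or the full protocol may show at once which score has an SD of 13.6. Naming a single primary scale is often left to an analysis plan, and the arithmetic is correct at the stated SD.

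Much of this stands, and it rules out several stronger readings that a reader might infer:

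- *That the study is sized on a score it will never obtain.* The documents do not show this. The Language Scale at 6 months may be meant, and it will be obtained.
- *That 13.6 or 79 is wrong.* Nothing in the documents contradicts the SD, and 79 follows from the inputs. The other SDs above are illustrative only.
- *That the main infant result will be chosen between scales after the data are seen.* The ambiguity leaves room for that, but an analysis plan not shown here may fix the score.

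The objection does not remove the conflict between the label and the protocol's own list of scales. An outside source could explain that conflict, but the text would still need correcting. Nor does the objection reach the reversed direction or the sufficiency claim: even with the score properly named, a formula for the precision of one mean cannot show that the study is large enough to detect an association with adipokines or to address maternal depression.

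**Conclusion.** The point holds as a fault in the definition of the sizing variable and in the claim drawn from it. As written, the SD of 13.6 and the 3 points belong to no identifiable Bayley-III score, and the comparison is stated in the opposite direction to the rest of the protocol. No numerical error in the 79 is shown. If 13.6 is the SD of the intended score and 79 pairs complete, the calculation supports a mean score known to about ±3 points, and nothing beyond that. The Discussion's statement about the primary objectives is therefore not supported. These conclusions rest on the article's own description of the instrument and on its own formula. Which score was intended cannot be settled from the article.

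**What to change.** 1. In the Sample size section, name the one Bayley-III score, from those listed under outcome 1, and the visit (6 months) to which the SD and the 3 points refer.
2. Confirm the SD for that score from the cited source or from the cohort's own pooled 6-month data, and restate the 3 points in that score's units and in SDs.
3. State the direction as development score by milk adipokine, in line with the headings for outcome and exposure.
4. Reword the Discussion so that the calculation is said to support only the precision of that score's mean (about ±3 points with 79 completers if the SD is 13.6), and not sufficiency for all primary objectives such as maternal mental health.

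The cost is wording and perhaps one restated figure, which may be less favourable if the confirmed SD is larger. Recruitment reached 117 in July 2024, and the correction calls for no further enrolment.

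### The sample-size formula fixes the precision of one mean, so it does not show that 79 completers can detect a 3-point difference or that the sample suffices for the primary objectives

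*Protocol article*

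**What the plan says.** The Sample size section of the protocol article opens by asking how milk adipokines differ according to infant development. It takes a Bayley-type score as its reference: "the reference was the global score of cognitive development in the communication domain". The target is worded as detection: "We will consider a difference of 3 points significant, and we aim for a significance level of 5% to detect differences if they exist". The spread is borrowed: "A previous study assumed that the standard deviation of the score is 13.6 for children of 6 months". The number then comes from a formula for a different task: "Applying the formula for determining the sample size based on an estimate of the population mean", that is n = [(Zα/2·σ)/e]², with inputs and result "1.96, e = 3 and σ = 13.6 (standard deviation), we obtain N = 79". An allowance of about 35% for loss to follow-up brings this to 117 pairs. The section gives no power and defines no groups or exposure contrast.

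The Discussion relies on the result when it lists limitations: "While the sample size is sufficient for the primary objectives of the project (as indicated by the sample size calculation". It then confines the raised risk of type II error to some of the specific objectives.

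**The concern.** The 3 points are described as a difference to be detected but are used as e, the half-width of a confidence interval for one mean. None of the objectives in the Abstract is to estimate a mean Bayley score. They are a plasma–milk correlation and associations of adipokines with neurodevelopment and with maternal mental health. The Data entry and statistical analysis section plans t-tests or ANOVA, Pearson correlation and a confounder-adjusted mixed model, and the formula sizes none of these.

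The Discussion gives the figure its weight. If readers accept that the calculation established sufficiency, a null association with neurodevelopment will be read as coming from a study sized to find 3 points. The calculation gives no such assurance.

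**Working it through.** **Inputs from the Sample size section:** two-sided 5% (Z = 1.96), SD 13.6, 3 points, 79 completers, 117 recruited, about 35% loss. **My assumptions:** a power target of 80% (Z sum 1.96 + 0.8416 = 2.8016), and each contrast below, because the article states neither.

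**1. The plan's own figure.** (1.96 × 13.6 / 3)² = 78.95, rounded up to 79. It reproduces.

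**2. What 79 delivers.** The half-width for one overall mean is 1.96 × 13.6 / √79 = 3.0 points. For a difference between two equal halves of 79 it is 1.96 × 13.6 × √(4/79) = 6.0 points.

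**3. Why the formula carries no useful power.** Even for the task closest to it, testing a 3-point shift of one mean, power is Φ(3√79/13.6 − 1.96) = Φ(0.00) = 50%. With the power term added, n = (13.6 × 2.8016 / 3)², which rounds up to 162.

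**4. Continuous exposure, closest to the planned analysis.** Suppose 3 points is the effect per 1 SD of adipokine. Then r = 3/13.6 = 0.2206 and, by Fisher's z, atanh(r) = 0.2243.
- Power at 79: Φ(0.2243 × √76 − 1.96) = 49.8%.
- Completers for 80%: (2.8016 / 0.2243)² + 3 = 159.04, rounded up to 160.
- Detectable at 79 with 80% power: r = tanh(2.8016/√76) = 0.311, or 0.311 × 13.6 = 4.2 points per SD.
- A 35% loss from 117 leaves 117 × 0.65 = 76. At 76, power for r = 0.22 is 48%, and the detectable r is tanh(2.8016/√73) = 0.317, or 4.3 points per SD.
- If all 117 were evaluable, power for r = 0.22 would be 67%.

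**5. Upper bound from repeated measures.** Bayley is given at 6 and 12 months. If the two visits were fully independent, with the same SD and the same effect, the effective number would be 158. Power is then Φ(0.2243 × √155 − 1.96) = 79.7%. Scores from the same child are normally correlated, so the true value lies below this.

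**6. Equal halves by adipokine level (not the planned main analysis).** Power is Φ(3 / (13.6 × √(4/79)) − 1.96) = 16.4%, or 16.2% with the t distribution. For 80%, 2 × 2.8016² × 13.6² / 9 = 322.6, so 323 per half.

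| Reading of the 3 points | Power at 79 |
|---|---|
| Equal halves | about 16% |
| Shift of one mean | 50% |
| Per 1 SD of adipokine, one visit | 50% |
| Per 1 SD, two visits fully independent (upper bound) | just under 80% |

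None of these figures allows for the planned confounder adjustment, which commonly widens the standard error of the exposure effect.

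**The case against.** The strongest reply is that an unsupported statement is not a false one. A reader might infer that the sample is too small and the sufficiency statement is therefore untrue. The documents do not settle that. The Discussion speaks of primary objectives in the plural, whereas the checks here concern one Bayley association and say nothing about the plasma–milk correlation or maternal mental health. With 79 completers an association of r about 0.31 or more is detectable at 80% power, so a larger true association could be found. A smaller exposure contrast also changes the answer: if 3 points went with half an SD of adipokine, r would be 6/13.6 = 0.44 and power at 79 would be Φ(0.474 × √76 − 1.96), about 98%. The article states no contrast, so neither adequacy nor inadequacy can be shown.

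A reader might also take the 16% figure as the main result and conclude that a null finding is the likely outcome even if a 3-point effect is real. That holds only under a split into halves. The Data entry and statistical analysis section analyses adipokines and development scores as continuous variables and assigns their association to a mixed model. On the continuous, one-visit reading, a null is about as likely as not.

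Finally, the Discussion already names the small sample as a main limitation and presents the study as hypothesis-raising. This softens the risk of over-reading a null, but it does not remove the point: the type II caveat leaves out the primary objectives precisely because the calculation is said to cover them.

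**Conclusion.** The concern holds in this form: the calculation does not support the claim built on it. The figure of 79 is correct as the number needed for ±3 points around one mean. It is not evidence that a 3-point difference linked to adipokines can be detected, and it cannot show sufficiency for objectives that are all correlations or associations.

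The size of the shortfall depends on a contrast that the article does not define. At SD 13.6 and two-sided 5%, power at 79 for 3 points is about 50% per SD of adipokine, about 16% for equal halves, and just under 80% at the upper bound for two visits. These are illustrations under stated assumptions, unadjusted for confounders. They do not prove that the study is inadequate for every effect of interest.

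A secondary point of clarity: the reference score is described as both cognitive and communication, while the Infant neurodevelopment section lists Cognitive and Language as separate Bayley scales and mentions communication under both Language and Adaptive Behavior. The article does not make clear which scale the SD of 13.6 belongs to. The stated question also concerns differences in adipokines, while the SD is that of a development score.

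**What to change.** In the Sample size section, replace the detection claim with wording such as:

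> 79 completers estimate the mean score to within ±3 points (95% confidence). For the association analysis, 79 completers (76 after 35% loss from 117) give 80% power at two-sided 5% for a correlation of about 0.31 (0.32), i.e. about 4.2 (4.3) points per SD of adipokine, as an unadjusted approximation at one visit.

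Name the Bayley scale to which the SD of 13.6 refers.

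In the Discussion, replace the sufficiency statement with this detectable effect, and extend the type II error caveat to the primary objectives.

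The cost is a text change only. The Methods state that recruitment reached its target in July 2024, and no participants, data collection or analyses need to change. The downside is that the stated sensitivity becomes less favourable than the present wording suggests.
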